### Monitoring

#### Data monitoring

A data monitoring committee (DMC) will not be established for several reasons. First, periodic inspection does not seem justified as trial duration is short (4 weeks). Second, overall risk associated with the self-help intervention is considered low, and therefore, the likelihood for the need to modify or discontinue the trial is considered insignificant. However, precautions have been taken to minimize the potential of any harm towards individual study participants, as detailed below.

#### Harms

Preventively, we will only enroll study participants without severe posttraumatic and/or depressive symptomatology and acute suicidality. The self-help program targets individuals with mild to moderate symptom severity. Despite these precautions, the occurrence of negative effects during the trial in individual cases cannot be entirely ruled out. Therefore, potential negative effects will be monitored through a standardized assessment procedure at follow-up 1 (post-intervention) and follow-up 2 (four months after baseline). Negative effects are defined as adverse events (AE) and severe adverse events (SAE). Specifically, AE comprise i) an increase in target symptoms (posttraumatic and depressive symptomatology, suicidality), ii) the occurrence of novel psychological or physical symptoms, and iii) any negative events, all of which may or may not be associated with trial participation, in both IG and CG. Participants will be questioned whether any AE is thought to emerge from trial participation. SAE are defined as severe negative events that occur during study participation and result in adverse reactions requiring some form of high intensity treatment (i.e., deliberate self-harm, suicide attempt, life-threatening events, non-elective or extended hospitalization, an event causing chronic or serve disability) or fatality, including suicide. SAE will be surveyed and reported regardless if they are deemed related to the trial or not. The principle investigator ([name]) will be immediately informed about the occurrence of any AE and SAE. Likewise, a consensus conference (incl. the principle investigator and clinical investigators) will be held immediately to decide on appropriate measures in response to AE and SAE. Moreover, data collected on AE and SAE will be analyzed and reported as part of the study outcomes.

Practically, during the trial, study participants of both groups (IG and CG) will be provided with detailed information regarding emergency hotlines and professional help, if needed, i.e., in case of unexpected symptom deterioration. The IG will have access to this information via an emergency button leading to a help menu within the app. The CG receives the same information as part of the psychoeducational reading material that is handed out at baseline. In addition, study participants of both groups will be encouraged to contact our study nurses if they need further support to find emergency help.

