#### Study adherence

Prior to randomization, participants will be pointed towards the required investment of time and effort necessary to complete the study in order to lower the risk for dropout.

Treatment adherence of the IG will be objectively assessed through the apps’ meta-data log-files that store information about the number of login-times and worked-through modules. Likewise, dropout assessment will be conducted to understand reasons for non-adherence.

Participants of both groups are assured to contact the study nurses in case of arising problems regarding current symptom burden, for example. Similar to the apps’ emergency button, the psychoeducational reading material will clearly state contact information regarding professional help in case of emergency.

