#### Sample size

Anticipated sample size was calculated based on recent research evaluating the efficacy of telemedical-based treatment of posttraumatic stress symptoms [20, 21, 38]. Given a moderate between-group effect at T1 (Cohen’s *d* = 0.5), a significance level of *α* = 0.05 and a statistical power of 1-*β* = 0.90, optimal sample size for estimating a significant treatment effect is *n* = 140. Expecting a drop-out rate of approximately 40% (e.g. due to change in residence status), *n* = 94 participants have to be included additionally, yielding an ideal baseline sample of *n* = 234 participants at T0 [39].

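### The standardized harm assessment is described only for the T1 and T2 interviews, so up to about 40% of participants may have no systematic AE/SAE data

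*Protocol article*

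**What the plan says.** **Schedule of harm assessment.** The Harms section states that "potential negative effects will be monitored through a standardized assessment procedure at follow-up 1 (post-intervention) and follow-up 2 (four months after baseline". It covers worsening of posttraumatic, depressive or suicidal symptoms, new symptoms, other negative events and SAEs. The resulting data are to be analysed and reported with the study outcomes. According to Data collection, every assessment is a face-to-face interview led by a study nurse. In Table 1 (Outcomes), the PDS-5, PHQ-9 and DSI-SS are scheduled after baseline only at T1 and T2.

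**Expected loss.** The Sample size section says "Expecting a drop-out rate of approximately 40% (e.g. due to change in residence status", and that 94 "participants have to be included additionally, yielding an ideal baseline sample of" 234. The calculation starts from "Given a moderate between-group effect at T1". When the dropout is expected is not stated.

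**Contact with those who leave.** Study adherence says "dropout assessment will be conducted to understand reasons for non-adherence". Data collection names negative effects and dropout reasons in one sentence, as two separate items. Neither section says that harm questions are put to people who drop out.

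**Other routes.** Under Harms, the principal investigator is told at once of any AE or SAE, and SAEs are reported whether or not they are thought related to the trial. Participants in both arms may turn to the study nurses (Study adherence; Harms).

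**The concern.** A harm comparison between arms needs the same questions put to comparable people in both arms. Here the questions are tied to attendance at two interviews in a trial that expects heavy loss. The section on expected benefits and harms accepts that trauma content may at first stir up distressing memories. Worsening is therefore a possible reason for leaving, and the app and the brochure need not act alike in this respect. If so, the people with no structured harm record would include some in whom harm is most likely.

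The protocol plans no data monitoring committee and relies instead on the precautions in the Harms section. It also intends to release the app freely to the public after evaluation. The trial's own AE and SAE data will then be an important part of the safety evidence.

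**Working it through.** **1. Reproducing the plan's figures.** Inputs from Sample size: 140 participants needed for the T1 comparison (taken as given here) and 40% dropout.

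- Baseline sample = 140 / (1 − 0.40) = 233.3, rounded up to 234. This agrees with the plan.
- Expected loss = 234 − 140 = 94, and 94 / 234 = 40.2%.

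**2. How many may have no structured harm assessment.** A participant interviewed at T1 or at T2 has at least one standardized harm record. The group without any record is those who miss both. Let f be the share of dropouts who leave before T1 and do not return for T2. The number unassessed is 94 × f. The protocol does not give f, so a range is shown:

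- f = 100%: 94 of 234 (40.2%)
- f = 75%: 70 of 234 (29.9%)
- f = 50%: 47 of 234 (20.1%)
- f = 25%: 24 of 234 (10.3%)
- f = 0%: 0 of 234

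The top of the range is a natural reading, because the 140 are those needed for the T1 effect. It remains an upper bound on the plan's expected dropout: some may leave between T1 and T2, and nothing bars a person who missed T1 from attending T2.

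**3. What the loss could do to a harm rate.** Let u be the unassessed share of an arm, a the harm risk among those assessed and m the risk among those not assessed. If nothing is learned about the unassessed:

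- rate in all randomised = (1 − u) × a + u × m
- rate observed = a
- shortfall in that arm = u × (m − a)

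The bias in the difference between arms is the IG shortfall minus the CG shortfall. It is zero if the unassessed have the same risk as the assessed, or if the shortfall is equal in both arms. For scale, suppose that m exceeds a by 10 percentage points in one arm only (an assumed figure). With u = 94/234 the difference is off by 0.402 × 10 = 4.0 points. With u = 47/234 it is off by 0.201 × 10 = 2.0 points. Nothing in the protocol gives m, a or the dropout in each arm, so these are multipliers and not estimates.

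**4. Whether another provision fills the gap.**

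- *Notification of the investigator:* this says what follows once staff know of an event, not how they learn of one in a person who no longer attends.
- *Reporting SAEs regardless of relation:* this concerns attribution. It adds no time point.
- *Contact with the nurses:* open to both arms, but it depends on the participant coming forward. It can reveal individual events but does not give rates on a common basis.
- *Dropout assessment:* it may reach the right people, but its stated content is reasons for stopping.
- *Multiple imputation and the drop-out analysis (Statistical analysis):* neither is tied to harms. Imputation from those who stayed would not in general recover harm that caused people to leave.

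**The case against.** The strongest reply is that this is a condensed article. The Harms section does not say that harms are recorded at no other time, and the form used at the dropout contact may be set out in a fuller protocol. Someone asked why they left may well report worsening. Nurse contact and immediate notification are not confined to people who attend interviews. Stopping use of the app is also not the same as missing an interview. The reasons for loss that the protocol names, a change in residence status and imminent deportation, have little to do with which arm a person is in. And people who have moved or been deported are often those whom a dropout contact cannot reach.

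Much of this stands, and it rules out three stronger readings that a reader might infer:

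- *That the harm comparison covers only those who stayed.* The protocol names no completer set for harms, and its unstandardized routes may capture events in people who leave.
- *That about 40% will have no structured harm data.* This requires all dropout to fall before T1 with no return at T2, which the protocol does not state.
- *That real excess harm from the app would show as no difference.* This needs assumed risks among the unassessed and no spontaneous reports from them.

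The objection does not remove the core. The article itself fixes when the standardized procedure is applied and states the purpose of the dropout assessment, and the two are not joined. The residence example is introduced as an example only, so it does not exclude leaving because of distress.

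**Conclusion.** The point holds as a gap in a stated schedule. Participants who miss both T1 and T2 have no described structured harm assessment and are left with spontaneous or other unstandardized reports. On the plan's own dropout figure this is at most 94 of 234 (40.2%), and about 47 (20.1%) if half of the dropouts leave before T1. Bias in the harm comparison requires two further conditions: that leaving is related to worsening, and that this differs by arm. Both are plausible, but neither is established, and the size of any bias cannot be derived from the documents. This is a worthwhile low-cost improvement. It does not show that the planned harm reporting is invalid.

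**What to change.** In the Harms section, make the dropout assessment already planned under Study adherence and Data collection an additional point of the standardized negative-effects procedure, with the same AE/SAE questions asked in both arms. In the report, give harms per arm with the number actually assessed as denominator, and list all known SAEs for everyone randomised.

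The cost is a few existing questions added to a contact that is already planned, and a clear denominator in the harms table. The dropout contact takes slightly longer. Dropouts who cannot be reached will remain unobserved, so the change narrows the gap without closing it; reporting the number assessed per arm shows how much remains.

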**Methods:**

We will develop a modular, interactive self-help app in Arabic, which will be grounded on cognitive-behavioral models for the treatment of posttraumatic stress. Subsequently, screened positive (i.e., Syrian refugees, 18–65 years old, mild to moderate posttraumatic stress symptomatology as quantified by the Posttraumatic Stress Diagnostic Scale for DSM-5/PDS-5) participants (ideally up to *n* = 234) will be randomly allocated to an intervention (IG) and control group (CG), respectively. Participants in the IG will gain access to the self-help app for one month, while participants in the CG will receive psychoeducational reading material in form of a comprehensive brochure on traumatization and posttraumatic stress. Measurements are scheduled before the intervention (T0), directly after the intervention (T1, one month later) and three months after the intervention (T2). Using linear mixed effect models, we will investigate change in posttraumatic symptomatology. We will also test for changes in secondary outcomes such as depression, anxiety, and quality of life. Moreover, we will inspect the usability and user acceptance of the app. To evaluate the app in terms of its economic health benefit, the incremental cost-effectiveness ratio will be calculated.

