### Expected benefits and harms

We expect that the low-threshold app-based intervention will lower posttraumatic symptom severity and associated secondary outcomes in favor of overall improved wellbeing and quality of life. Furthermore, since our self-help app will be in Arabic language, basal information regarding treatment options and disease management can be provided to a broad group of traumatized refugees without causing costs due to translation. This can help to compensate for the lack of adequate psychotherapeutic care for Syrian refugees in Germany. In case of an unexpected increase in symptom severity - the trauma-related content might initially trigger unpleasant memories and feelings - both study groups will be provided with contact information for professional help in case of emergency. Moreover, the occurrence of negative effects, regardless whether or not related to the trial, will be monitored.

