#### Usability

To maximize usability, content related materials will be provided in Arabic. Moreover, the app will additionally be complemented by video and audio sequences as well as interactive games and exercises. All submodules will be available at all times, giving users the possibility to flexibly switch between sections depending on their personal needs. The app will also provide a clearly visible emergency button with contact information regarding professional help in case of emergency. The app will be usable offline.

With respect to the technical implementation, the app development will take place in cooperation with the e-mental health program provider “Frühlingsproduktionen”.

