#### Intervention

The apps’ efficacy and usability as well as the overall associated cost effectiveness of the intervention will be evaluated in a prospective RCT with an IG and a CG (see Fig. 2). Following the initial screening and study group assignment, participants in the IG will gain access to the self-help app via person-specific log-in data (to avoid group contamination) for one month. During that time, the CG will obtain psychoeducational reading material about traumatization and posttraumatic stress (identical to the information delivered by the app) in form of a comprehensive brochure in Arabic.

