#### Timeline

After positive screening, study participants will be enrolled. Measurements are scheduled directly before the intervention (baseline, T0/pre), immediately after the intervention (T1/post, one month later), and three month after the intervention (T2/follow-up) to test for medium-termed treatment effects. A detailed overview of the schedule of enrolment, interventions and assessments is given in Fig. 3.

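### If app access ends at one month as stated, the intervention group loses its only named written source of emergency contacts for about 12 of the 16 weeks to the last harm assessment

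*Protocol article*

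**What the plan says.** The section on expected benefits and harms makes a general promise: "both study groups will be provided with contact information for professional help in case of emergency". It sets no time limit and names no carrier.

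The carriers are named elsewhere, arm by arm:

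- **IG.** Usability states: "The app will also provide a clearly visible emergency button with contact information regarding professional help in case of emergency". Harms repeats this as the IG's route: "The IG will have access to this information via an emergency button leading to a help menu within the app".
- **CG.** Study adherence states that "the psychoeducational reading material will clearly state contact information regarding professional help in case of emergency". Harms adds that this material is given out at baseline.

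App access is limited in time. The abstract says "Participants in the IG will gain access to the self-help app for one month", and the Intervention section says that IG participants "gain access to the self-help app via person-specific log-in data (to avoid group contamination) for one month". Usability also says: "The app will be usable offline".

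Follow-up runs longer than app access. Timeline places the last assessment "three month after the intervention (T2/follow-up) to test for medium-termed treatment effects", and the Fig. 3 caption puts it 16 weeks after baseline. Harms schedules the standardized assessment of negative effects after the intervention and again four months after baseline. Increased suicidality counts there as an adverse event, and self-harm and suicide attempts count as severe adverse events.

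Both groups are also told that they can turn to the study nurses (Study adherence, Harms).

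**The concern.** Three things the article fixes do not fit together: the carrier of the IG's emergency contacts (the app), how long that carrier is available (one month), and how long participants are monitored for harm (four months). Read as written, the IG's named written source of help stops at T1 while the CG keeps its brochure.

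What is at stake is participant safety, not the comparison. Current psychotherapy or psychiatric treatment is an exclusion criterion, so participants enter without a treating clinician. The article itself allows that the trauma content may at first stir up distressing memories. The Data monitoring section declines a monitoring committee partly because precautions for individual participants are in place, and the emergency information is one of them. That section also calls the trial four weeks long, which suggests that the safeguard was planned around the app month and not around the full follow-up.

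An IG participant who deteriorates between T1 and T2 would have to reach a study nurse or rely on contacts noted earlier.

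**Working it through.** **Inputs**

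| Input | Value | Where |
|---|---|---|
| IG app access | one month, by personal log-in | Abstract (Methods), Intervention |
| T1 | 4 weeks after baseline | Fig. 3 caption |
| T2 | 16 weeks after baseline | Fig. 3 caption |
| Last harm assessment | four months after baseline | Harms |
| Assessments after baseline | T1 and T2 only | Timeline |
| Ideal sample | 234 | Sample size |
| Allocation | 1:1 | Allocation and randomization |

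**Step 1: reproduce the plan's own timing.** T2 is three months after a one-month intervention. Counting the intervention as 4 weeks and the three months as 12 weeks gives 4 + 12 = 16 weeks, which matches Fig. 3. In calendar months it is 1 + 3 = 4 months, which matches Harms. At about 4.35 weeks per month, that is about 17.4 weeks. The two descriptions agree apart from rounding.

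**Step 2: length of the interval without the named carrier.**

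- Fig. 3 schedule: 16 − 4 = 12 weeks; 12/16 = 75%.
- Calendar months: 4 − 1 = 3 months; 3/4 = 75%, or about 13.0 of 17.4 weeks.

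**Step 3: scheduled contact in that interval.** T1 opens it and T2 closes it, so there are 0 scheduled assessments between them.

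**Step 4: participants affected.** At 1:1 allocation, 234/2 = 117. I make no deduction for the expected 40% dropout, because someone who leaves the assessments may still need the contacts. This is an upper bound: it assumes that the ideal sample is reached and that nobody holds another copy.

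**Step 5: the other end of the range.** If the help menu stays usable to T2, or if IG participants hold the contacts in another form, the gap is 0 weeks.

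**Side by side**

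| | Weeks 0–4 | Weeks 4–16 |
|---|---|---|
| IG: named written carrier | in-app help menu | none stated |
| CG: named written carrier | brochure | brochure |
| Study nurses, both groups | yes | yes, no end date stated |

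**The case against.** The strongest reply is that the article nowhere says the emergency information is withdrawn. One month may simply define the intervention dose, and the stated purpose of the personal log-in is to keep the CG out. An app that works offline may stay on the phone with its menu reachable. The general promise to both groups has no time limit, and naming the button does not make it the only means of delivery. Consent and participant information are not visible, and a journal article commonly leaves contact sheets and app settings to the full documents.

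The interval is also not unprotected. Arabic-speaking nurses can be contacted by both groups. IG participants who attend T1 are seen face to face just as the gap would open, with a suicidality scale and a negative-effects assessment. Severe posttraumatic or depressive symptoms and acute suicidality are excluded at entry. Finally, no estimate, test or power figure is touched.

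Much of this stands. The loss is inferred, support does not lapse altogether, and the true gap may be zero. Three things remain:

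- Offline use is about connectivity; no section says that the help menu stays open after the month.
- Harms sets out delivery arm by arm and mentions no sheet common to both groups.
- Harms offers the nurses as an addition, to help participants find emergency care. They are not described as a replacement for the written contacts.

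The T1 visit would be a good moment to hand over the contacts, but the article does not say that this happens.

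**Conclusion.** The point holds in its conditional form, as a minor safety matter to consider, with low confidence that any participant is actually left without written contacts. If access to the help menu ends with the app month, the IG's named written carrier covers 4 of the 16 weeks to the last harm assessment and is missing for the other 12 (75%), for up to 117 participants, while the CG's brochure has no stated end. The full range is 0 to 12 weeks, and the article alone cannot place the truth within it.

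The conclusion assumes that the one-month limit applies to the whole app including its help menu, and that no other written copy was issued. It does not claim that participants have no help at all, and it does not claim bias in any group comparison.

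**What to change.** Give each IG participant the same emergency-contact page that the CG receives, at baseline or at the latest at the face-to-face T1 visit. Baseline is better, because it also reaches those who miss T1. Alternatively, keep the app's help menu open through T2. State the choice in the Harms section. If either arrangement already exists, stating it there is enough.

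The cost is one sentence, plus either one printed page per IG participant (up to 117 pages) or one app setting. No extra staff or visits are needed. The contrast between the groups is unaffected, since the CG already holds the same contacts.
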